##### e) Cost effectiveness

We have not powered our trial for the cost-effectiveness outcome because we expect the intervention to be dominant as compared to the usual care, i.e. improved outcomes *and *lower costs. Thus, additional resources required to implement the intervention are expected to be fully or partially offset by reduced consumption and associated costs of other health care services (especially outpatient attendance for somatic symptoms) and to also lead to reduced opportunity costs to patients and families (especially lost work days). This is what we found for the antidepressant arm in the earlier cost-effectiveness trial in Goa [16].

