For the economic analysis, health care costs and other patient- or family-borne costs will be computed and compared at 2, 6 and 12 months, and subsequently related to changes in health outcome: both the primary outcome measure of depression status and also Quality Adjusted Life Years (QALYs). A culturally specific and conceptually solid utility measure for depression – necessary for the estimation of QALYs – will be generated by relating health state valuation scores (taken from an Indian population as part of a wider WHO multi-country study) to summary scores on the WHO-DAS. In the event that dominance is not shown, i.e. the intervention is more effective but the costs are also more than the usual care group, we will estimate the probability of dominance and estimate incremental net benefit and incremental cost-effectiveness ratios. The latter will be computed, together with their confidence intervals (using bootstrapping techniques to overcome expected skewness of cost data). Cost-effectiveness acceptability curves will also be derived in order to show the probability of any cost-effective advantages for the component interventions at a range of 'willingness to pay' threshold levels.

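### The probability of dominance and incremental net benefit are planned only if dominance is not shown, so a claim of better and cheaper could be made without them

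*Protocol article*

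**What the plan says.** The economic paragraph of Data management & analyses starts without a condition: "health care costs and other patient- or family-borne costs will be computed and compared at 2, 6 and 12 months", and these are then related to health outcome. The next analytical step is conditional. It applies "In the event that dominance is not shown, i.e. the intervention is more effective but the costs are also more than the usual care group", and in that event "we will estimate the probability of dominance and estimate incremental net benefit and incremental cost-effectiveness ratios". Bootstrap intervals come next: "The latter will be computed, together with their confidence intervals (using bootstrapping techniques to overcome expected skewness of cost data"). The closing sentence, "Cost-effectiveness acceptability curves will also be derived", does not repeat the condition. It describes the curves as being for the component interventions.

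Sample size, e) Cost effectiveness gives the background: "We have not powered our trial for the cost-effectiveness outcome because we expect the intervention to be dominant as compared to the usual care". It explains that the added resources "are expected to be fully or partially offset by reduced consumption and associated costs of other health care services", and that opportunity costs to patients and families, chiefly lost work days, should also fall. It adds: "This is what we found for the antidepressant arm in the earlier cost-effectiveness trial in Goa".

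**The concern.** The probability of dominance is most needed when someone wants to claim dominance. As written, it is promised only in the other case. Incremental net benefit is tied to the same condition and, on the natural reading, so are the bootstrap intervals. The gloss on the condition refers only to which arm is more effective and which costs more. A small and imprecise saving would therefore be enough to leave the branch in which uncertainty is quantified.

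Cost-effectiveness is half of the hypothesis in Aims. The Background says scale-up may turn on it, and the Discussion calls such data critical for health ministries. A statement that the intervention is both better and cheaper would be a headline policy message, and it could rest on the sign of a skewed cost difference estimated from 24 facilities.

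**Working it through.** **What is conditional.** Setting the sentences of the economic paragraph side by side:

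- Not conditional: costs computed and compared at three time points, and related to outcome. No measure of joint cost and effect uncertainty is named here.
- Conditional: probability of dominance, incremental net benefit and the ratios.
- Conditional on the natural reading: the bootstrap intervals. They attach to the quantities just named, though the wording could mean the ratios alone, which are themselves conditional.
- Unclear: the acceptability curves. They follow in the same run of text without restating the condition, and they refer to components, whereas the randomised contrast is collaborative stepped care (CSC) against enhanced usual care (EUC).

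**How secure the expectation of dominance is.**

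- For: the antidepressant arm of the earlier Goa trial; the Background's report of lower total health care costs in the Indian trial; expected savings in lost work days.
- Against: the CSC section takes its model from the Chilean trial, for which the Background reports an additional cost per depression-free day. The EUC section has project fluoxetine supplied to primary health centres in both arms, so in those 12 facilities its supply is not what differs between arms.
- Weaker: the Background expects increased investment, and Ethical considerations mentions additional costs. Both can be read as costs before any offset, so they do not exclude a net saving.

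**Size, as an illustration.** The article gives no cost difference, cost variance or power for this outcome, so there is no figure to reproduce.

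Inputs from Sample size, a): 150 screen-positive participants per facility and up to 25% lost. That gives 150 × 0.75 = 112.5 per facility and 112.5 × 12 = 1350 per arm. The article does not fix the economic analysis population; all followed screen-positives are assumed.

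Assumed, not in the documents: cost coefficient of variation (CV) 1 to 2, and cost intracluster correlation (ICC) 0.01 to 0.05.

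Standard error of the cost difference, as a share of mean cost: SE = CV × √[2 × (1 + 111.5 × ICC) / 1350].

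- CV 1, ICC 0.01: 1 × √(2 × 2.115 / 1350) = 5.6%.
- CV 2, ICC 0.05: 2 × √(2 × 6.575 / 1350) = 19.7%.

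Chance that the estimate shows a saving, by normal approximation: Φ(−true excess / SE).

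| True cost excess of CSC | SE 5.6% | SE 19.7% |
|---|---|---|
| 0 | 50% | 50% |
| 5% | Φ(−0.89) = 19% | Φ(−0.25) = 40% |
| 10% | Φ(−1.79) = 4% | Φ(−0.51) = 31% |

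Using only the 75 definite cases per facility (900 per arm) changes little: SE 6.2% to 20.4%, with 21% to 40% for a 5% excess and 5% to 31% for a 10% excess.

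These are chances of an observed saving. Dominance also needs a better outcome, so they are upper bounds for the dominant quadrant. The bound is close if the clinical effect is as large as planned.

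**What the missing figure would show.** An observed saving of 0.25, 0.5 or 1 standard error corresponds to a probability of lower cost of Φ(0.25) = 60%, Φ(0.5) = 69% or Φ(1) = 84%. A reader told only that the intervention was dominant would not see this.

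**The case against.** Several stronger readings are tempting, and the text does not support them.

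- A reader might infer that every chance saving would be reported as dominance. The article does not say that point estimates decide. Shown is undefined and may be meant statistically, and planning a probability of dominance suggests a probabilistic view. Only that it could be so reported stands. If a statistical meaning was intended, the directional gloss needs correcting anyway.
- A reader might infer that no uncertainty at all is reported when costs come out lower. The cost comparison is unconditional, and the acceptability curves may be. That cannot be settled from the text.
- A reader might take a partial offset as contradicting dominance. The same sentence goes on to expect lower opportunity costs, and the plan counts patient and family costs. A partial offset in health care costs can still leave a lower total.
- A reader might say that the fluoxetine supply removes the Goa precedent altogether. It applies to the primary health centres only, which are half of the facilities, and supply is not use. CSC adds a counselor and adherence management, so adequate treatment may still differ between arms.

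It is also sound to confine the ratio to cases where it can be interpreted; a negative ratio under dominance is not useful. How the remaining quadrants are handled, and the interval for the plain cost comparison, are details that a condensed article may leave to a fuller plan.

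What remains is a stated rule, not an omission: net benefit and the probability of dominance depend on the observed result.

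**Conclusion.** The point holds in limited form. The economic paragraph makes the probability of dominance and incremental net benefit, and on the natural reading the bootstrap intervals, depend on dominance not having been shown. Dominance could therefore be claimed without them, in an analysis that was not powered. The expectation of dominance has some support in the article but is not secure; it would go too far to say the article gives no grounds for it.

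That the rule depends on the result follows from the wording alone. The size does not: 19% to 40% for a true 5% excess rests on the assumed cost variation and intracluster correlation, on a normal approximation, and on the choice of analysis population. The primary clinical analysis is unaffected. What is exposed is a policy claim that the article treats as important.

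**What to change.** In Data management & analyses, remove the condition for everything except the ratio. Whatever quadrant the estimates fall in, report for CSC against EUC:

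- incremental cost and incremental effect, with bootstrap intervals that respect clustering by facility;
- incremental net benefit with its interval over a stated range of thresholds;
- the probability of dominance;
- an acceptability curve for the randomised contrast, not for components.

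Give the incremental cost-effectiveness ratio only where it is interpretable.

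In Sample size, e) Cost effectiveness, stop using expected dominance as the reason for not considering precision. Say that the economic result is an estimate with the precision that the design gives.

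The cost is a few sentences and a little analysis. Most of these outputs are already planned within one branch, and no further data or participants are needed.

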### Trial monitoring

The following 'sentinel' outcome data will be recorded upon completion of interviews for monitoring and safety requirements, and reported to the Trial Steering Committee and Data Monitoring & Ethics Committees at least quarterly: number and proportion of completed outcome assessments and refusals; ICD10 case status for any CMD and Depression; hospitalizations; suicide attempt; and deaths.

No stopping rules are proposed because serious adverse events are not expected in the trial since none of the treatments being offered are experimental or associated with serious outcomes. A recent systematic review has shown that RCTs stopped early show implausibly large treatment effects and that there needs to be a balance between the ethical concerns of safeguarding interests of patients who have been randomized in the trial while also "protecting society from overzealous premature claims of treatment benefit [64,65]." Furthermore, the trial will proceed to phase 2 (GP facilities) without conducting formal interim analyses at the end of phase 1 (PHC facilities) since, even if such analyses showed considerable impacts of the intervention, these may not be generalizable from PHC to GP facilities.

## Ethical considerations

While the efficacy of specific intervention components (e.g., anti-depressant drugs) is established in developing countries, the same is not true for the effectiveness of intervention strategies that attempt to introduce these into usual primary care. The proposed trial is addressing whether a collaborative stepped-care intervention enables these treatments to be provided effectively in primary care and, if so, what are the marginal benefits and costs. There is genuine clinical equipoise concerning this research question in the context of developing countries where the intervention presents additional costs and where there are several other public health priorities. Under-powered trials are unethical for patients [66]; our sample size calculations are therefore based on conservative estimates and high power. No participant will be deprived of any treatment s/he would ordinarily receive. Participants in the enhanced usual care control facilities may benefit as a consequence of the screening and, in the PHCs, the provision of antidepressants to the pharmacy. Thus they will be provided with the results of the screening questionnaire and those who remain ill at 12 months will be offered psychiatric consultation by the Clinical Specialist. In addition, if any trial participant (in either arm) is found to have attempted suicide (assessed during outcome evaluation), the field work team will report this through an administrator to the intervention team who will make arrangements to provide psychiatric care for the participant. Explicit referral guidelines will be provided to doctors in the Enhanced usual care control arm for patients who may be suicidal or need specialist advice (to the local public psychiatric services available in three hospitals in Goa).

In cluster RCTs, consent for participation in a trial is needed both from the clusters and, depending on the type of intervention being delivered and outcomes assessed, from individual participants. In the MANAS trial, cluster level consent is being obtained as follows:

• Phase 1: PHC consent has been obtained in two steps; first, the Government of Goa's Directorate of Health Services; after the final 12 PHCs were identified and randomized, specific written consent was obtained from the DHS for the participation of these 12 PHCs.

• Phase 2: Individual facility level consent from each GP is implicit since only those who are consenting to participate will be included in the sampling frame.

Individual participant consent is being obtained in two stages: after the screening, those who are screen-positives will be invited to participate in the CIS-R interview and thereby be enrolled in the trial; and for those selected for outcome evaluation, formal written consent will be obtained by the field researcher at the first visit to the participant in his/her home 2 months after enrollment.

Formal ethical approval has been obtained from the IRBs of the lead Goan organization (Sangath) and the London School of Hygiene & Tropical Medicine and has been approved by the Indian Council for Medical Research. The Trial Steering and Data Monitoring & Ethics Committees will monitor the progress of the trial. A fresh report will be made to both ethics committees of major changes in the protocol since the original proposal was assessed.

## Discussion

While there is evidence on *what *treatments work for CMD in developing countries, the question of *how *these can be effectively delivered in routine primary care remains unanswered [67]. This is one of the major research priorities in global mental health [68]. The results of the trial will be used to inform policy makers and practitioners in developing countries on the practical implementation, and the clinical and economic benefits of improving the management of CMD in primary care. The trial is likely to yield findings which are generalisable beyond the population of the study and, if effective, could be scaled up in health policy due to: the representative sampling of participants from rural and urban, private and public primary care facilities; the use of an intervention strategy which integrates evidence from efficacy trials from three developing countries and emphasizes acceptability (to practitioners, policy makers and participants), affordability (acceptable cost-effectiveness ratio) and availability (use of locally available resources); and the application of methods to address obstacles to the integration of mental health in primary care.

We acknowledge that the trial intervention will not tackle all the obstacles to the integration of mental health in primary care, such as the stigma associated with mental illness in the community [33,35]. Some components of the intervention may not seem generalisable. First, is screening a feasible component of the intervention? Recognition of CMD is an essential requirement for providing an intervention. A strictly naturalistic trial may have chosen to recruit subjects referred by the primary care doctor. We ruled this out since there is good evidence to show that recognition rates are very low [10,12,14,56] and that training doctors does not lead to sustainable higher rates of recognition[33]. Furthermore, a recent systematic review of collaborative care interventions found systematic identification of patients was one of only three specific ingredients which predicted a favorable response to the intervention [32]. Thus, screening in this trial is an integral component of the intervention as well as being used to identify a comparable sample of CMD patients in the Enhanced usual care control arm. With regards to scaling up, we believe that screening is feasible because of the high prevalence of CMDs in primary care attenders, the brevity of screening instruments (which may be reduced to just a couple of questions) [69] and the increasing literacy rates in many countries which makes self-completion feasible. The second component is that of the need for employment of a Health Assistant and a Health Counselor, additional human resources, in primary care facilities. However, the type of persons we will use in this role is relatively low-cost. Such persons who might suit these roles are easily available in most developing countries and could perform other roles, such as behaviour modification and lifestyle interventions for other chronic diseases. If Ministries of Health are to consider supporting mental health programmes which involve additional resources, data on the feasibility and cost-effectiveness of interventions are critical [34]; the proposed trial will provide the first systematic evidence of this kind from a low income country.
